## Abstract

**Background:**

Recent EAU guideline strongly recommended combined targeted biopsy (TBx) with systematic biopsy (SBx) for biopsy naïve patients with suspected multiparametric magnetic resonance imaging (mpMRI) lesions; However, the clinical goal is to find out how to determine the optimal SBx and TBx cores for biopsy in order to maximize the detection of csPCa and minimize the associated defects. This study aims to assess the efficacy and safety of the new biopsy strategy combining 6-core systematic and 3-core MRI- TBx compared to 12-core systematic and 3-core MRI-TBx strategy.

**Methods:**

This is a single-center, prospectively randomized controlled clinical trial. 280 men meeting inclusion criteria will be recruited and will be randomly allocated to either 6-core systematic plus 3-core MRI-TBx group (Group A) or 12-core systematic plus 3-core MRI-TBx group (Group B). The primary outcome compares the detection rate of PCa and clinically significant prostate cancer(csPCa) between group A and group B. The secondary outcomes compare the participant-reported pain score immediate post biopsy using pain measurement scale; proportion of men with post-biopsy complications and adverse events (Time frame: 7 days post biopsy, 30 days post biopsy); proportion of the men who undergo radical prostatectomy and have cancer upgraded histopathology from the biopsy to the radical prostatectomy.

**Results and Discussion:**

A new biopsy strategy should be developed with the goal of minimizing procedure invasion, our study will provide the results of efficacy and safety of the new biopsy strategy (6-core systematic and 3-core MRI-TBx) in biopsy naïve men with suspicious mpMRI lesion in comparison with 12-core systematic and 3-core MRI-TBx.

**Trial registration:**

Chinese Clinical Trial Registry, ChiCTR2200056437; http://www.chictr.org.cn/edit.aspx?pid=151413&htm=4

## Introduction

1.

Prostate cancer (PCa) is one of the most diagnosed tumor types among male worldwide, with an estimate of 268,490 new cases and 34,500 deaths in the United States in 2022 (1). Nowadays, for the detection of PCa in patients with a raised prostate-specific antigen (PSA) level, a standard 10–12 cores transrectal ultrasound-guided (TRUS) systematic biopsy (SBx) of the prostate is generally recognized (2). However, this approach might underdetect the clinically significant prostate cancers (csPCa) and overdetect the clinically insignificant cancers.

When the multiparametric magnetic resonance imaging (mpMRI) is widely applied, with the prostate imaging-reporting and data system (PI-RADS) version 2.0 developed in 2015 (3), MRI-targeted biopsy (TBx) has now been accepted and recognized because of its important value in the diagnosis of PCa, especially csPCa (4). In 2018, the PRECISION trial demonstrated that performing four TBx cores for lesions with positive mpMRI (PI-RADS >2) would possibly reduce overdiagnosis and subsequent overtreatment of clinically insignificant cancers while improving the detection of csPCa when compared to a standard 10– 12-core TRUS SBx (5). Though TBx has some benefits, this approach alone may also cause missed diagnosis of PCa, thus result in delayed treatment (6, 7). The 2021 European Association of Urology (EAU) guideline strongly recommended combining TBx with SBx for biopsy naïve patients with suspected mpMRI lesions (2).

However, the optimal cores for the combined systematic and TBx have not been fully investigated. In the era of mpMRI, our previously study found that for suspected mpMRI lesions, the third targeted core can increase the detection rate of csPCa by 11.5% (13.5–26.7%) based on the first two cores; however, the incremental value of adding the fourth or the fifth core was only 6.0% (range: 4.7%–6.9%) and 4.1% respectively (8). Song et al. also supported that a 3-core TBx per lesion was suitable during transperineal MRI ultrasound fusion biopsy. It is worthy of note that currently the SBx still applied the traditional scheme of 10- to 12 cores while adding to the combined biopsy strategy, which might overlap the mpMRI lesions and lead to the unnecessary repeat biopsies. Using as few biopsy cores as possible is likely to reduce procedure time and pathologists' workload and minimize patient discomfort as well as the incidence of complications (9). Therefore, the clinical goal is to figure out how to determine the optimal systematic and TBx cores for the current combined approach, which can maximize the detection rate of csPCa while minimizing the associated defects, especially in the setting of transperineal biopsy under local anesthesia.

Thus, this prospectively randomized controlled trial (RCT) aims to explore the efficacy and safety of the new biopsy strategy combining 6-core systematic and 3-core MRI-TBx compared to 12-core systematic and 3-core MRI-TBx. We will indicate whether 6-core systematic plus 3-core MRI-targeted prostate biopsy could be performed, thus, decreased SBx cores in the detection of csPCa.

## Methods and materials

2.

### Ethics and dissemination

2.1.

The study protocol has obtained the approval of biomedical ethics committee of West China Hospital (No. 2021-1649). The clinical trial registration has been completed at Chinese Clinical Trial Registry (No. ChiCTR2200056437). Participants will be required to provide the written informed consent forms to investigators before they are enrolled in the study. And they will also receive follow-ups from the investigators. The results of this study will be reported through national and international papers or conferences.

### Study design, randomization, and blinding

2.2.

Our protocol is a single-center, prospective RCT. Patients' demographic, clinical, and laboratory data will be obtained prospectively from electronic medical records of West China Hospital. We used a computer-generated random number to establish the randomization sequence. Eligible participants will be randomly allocated to either 6-core systematic plus 3-core MRI-TBx group (Group A) or 12-core systematic plus 3-core MRI-TBx group (Group B) with a ratio of 1:1 (Figure 1). In our trial, the urologist will not be blinded to any results because they will use the clinical and MRI findings to make clinical decisions and perform prostate biopsies.

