#### TRUS biopsy

2.4.2.

TRUS guided transperineal prostate biopsy will be performed under local anesthesia by experienced urologists. Three cores of cognitive fusion TBx were performed within the index lesion (defined as the lesion with the highest PIRADS v2 score, or the lesion with the maximal diameter if more than two lesions with the same score). Then, 6-core or 12-core SBx will be arranged for the patients according to the enrollment (Figure 2). The standard 12- core systematic sampling protocol will be performed transperineally with five cores distributed evenly through the left and right peripheral zones, and another core will be further spread on left and right transitional zones (10). Each core will be labeled independently and sent to histology using separate containers.

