#### Outcome

2.4.2.

The primary outcome compares the detection rate of PCa and csPCa between group A and group B where csPCa is defined using the Gleason scoring system (Gleason ≥3 + 4) (11). The secondary outcomes conclude as follow: (1) The yield of clinically significant prostate cancer on each side of prostate comparing it to side of lesions (contra- or ipsilateral to lesions). (2) The PCa and csPCa detection rate when adding transitional zone cores (11 and 12 cores in total). (3) The PCa and csPCa detection rate between Group A and 10-core SB plus 3-core TB in Group B. (4) The PCa and csPCa detection rate between transitional zone and peripheral zone in Group A and Group B. (5) Comparing the participant-reported pain score immediate post biopsy using pain measurement scale (Supplementary Figure S1). (6) proportion of men with post-biopsy complications and adverse events (Time frame: 7 days post biopsy, 30 days post biopsy), which include pain, fever, urinary infection/prostatitis needing antibiotics, urinary retention, erectile dysfunction, urinary incontinence, haematochezia, haematuria, and haemotospermia. (7) proportion of the men who undergo radical prostatectomy and have cancer upgraded histopathology from the biopsy to the radical prostatectomy (Table 1).

**Table 1 T1:** Schedule of record.

	Visit 0	Visit 1	Visit 2	Visit 3
Weeks	−1	0	1	4
Teleconsult	×		×	×
Inclusion/Exclusion	×			
Family history of prostate cancer	×			
Informed consent	×			
Age	×			
t-PSA level	×			
free/total PSA ratio	×			
mpMRI result	×			
Number of lesions	×			
Size of lesions	×			
Index lesion PIRADS score	×			
Biopsy outcome			×	
Benign tissue			×	
Atypical small acinar proliferation			×	
High-grade prostatic intraepithelial neoplasia			×	
Clinically insignificant cancer			×	
Clinically significant cancer			×	
Positive biopsy cores			×	
Gleason score			×	
Men who did not undergo biopsy		×		
Undergo surgery				×
Surgery outcome				×
Pathology Gleason score				×
Immediate post biopsy questionnaire (pain)		×		
Complications		×	×	×

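### No reason is given for the operator to know the arm, and no blinding to it is described, while the three targeted cores common to both groups are taken

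*Protocol article*

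**What the plan says.** Section 2.2 (Study design, randomization, and blinding) randomises eligible men 1:1 and then addresses the operator: "the urologist will not be blinded to any results because they will use the clinical and MRI findings to make clinical decisions". It does not say when the operator learns the arm.

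Section 2.4.2 (TRUS biopsy) gives the order of sampling. First, "Three cores of cognitive fusion TBx were performed within the index lesion". After that, "Then, 6-core or 12-core SBx will be arranged for the patients according to the enrollment". It adds: "Each core will be labeled independently and sent to histology using separate containers".

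The Outcome section defines the primary outcome as detection of PCa and csPCa in Group A against Group B. This is detection by the whole biopsy, so the targeted cores count in both groups. Table 1 has a Visit 1 row headed "Men who did not undergo biopsy".

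**The concern.** The sentence on blinding justifies one kind of knowledge (imaging and clinical findings) and is silent on another (the allocation). An operator needs the first in order to aim the targeted cores. The second is not needed until the systematic cores begin.

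The targeted cores are the part of the procedure most open to the operator's judgement. They are placed by cognitive fusion, without registration software, in a solitary lesion under 2 cm. An operator who knows that only six systematic cores will follow might place or spread the three targeted cores with more care than one who knows that twelve will follow. Any such difference enters the primary outcome directly.

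The trial asks whether fewer systematic cores suffice. Compensation in Group A would therefore favour the answer that the reduced template is adequate, and the estimate would no longer isolate the effect of the systematic template.

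**Working it through.** **1. What the sections support, side by side.**

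- Reason for not blinding (2.2): clinical and MRI findings. Allocation is not named.
- Timing of allocation: eligible men are randomised (2.2), and Table 1 places eligibility and consent at Visit 0, week −1, before the biopsy-day items at Visit 1. Allocation before biopsy is the natural reading, but no sentence states it.
- Order of cores (2.4.2): three targeted cores, then 6 or 12 systematic cores. The arm changes nothing until the third targeted core is done.
- Blinding of the operator to the arm: described nowhere.

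**2. The plan's own sample size.** Inputs from section 2.5: 61.2% (Group A), 64.5% (Group B), 80% power, one-sided 2.5%, 132 per group. A test for a difference between these rates needs 3,365 per group. The figure of 132 is reproduced by a non-inferiority formula if a margin M of 20 points is supplied. The article states no margin, so this is an assumption.

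n = (1.960 + 0.842)² × [0.612 × 0.388 + 0.645 × 0.355] / (0.20 − 0.033)² = 7.849 × 0.46643 / 0.02789 = 131.3, rounded up to 132.

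**3. What a shift towards Group A would do.** Let the true loss equal the margin, so Group A's true rate is 0.645 − 0.20 = 0.445, and let arm-dependent targeting raise Group A's overall detection by b. Then

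type I error = Φ(b / SE − 1.960), with SE = √{[0.645 × 0.355 + (0.445 + b)(0.555 − b)] / 132}.

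| b (points) | SE | b / SE | one-sided type I error |
|---|---|---|---|
| 0 | 0.0600 | 0 | 2.5% |
| 1 | 0.0601 | 0.166 | 3.6% |
| 2 | 0.0602 | 0.332 | 5.2% |

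Margins of 10 or 15 points give the same values to within 0.1 percentage point, so this result hardly depends on the assumed margin. The values of b are scenarios. The article offers nothing from which to estimate b.

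**4. The opposite direction.** If targeting were less careful in Group A, the error rate would fall and power would suffer. At the planned rates and M = 0.20, power is Φ(0.167 / 0.05944 − 1.960) = 80.2%. A shift of 1 point against Group A gives Φ(0.157 / 0.05958 − 1.960) = 75.0%, and 2 points give Φ(0.147 / 0.05970 − 1.960) = 69.2%.

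**5. Targeted yield against overall detection.** The b above is a shift in overall detection. A rise in targeted yield moves overall detection by less, because the systematic cores would have found some of those cancers anyway. Let T be targeted-only detection (not in the article; assumed 40% to 55%) and s = (0.612 − T) / (1 − T) the chance that Group A's systematic cores find a cancer that targeting did not. A rise d in T moves overall detection by d(1 − s).

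- T = 0.40: s = 0.353. A 3-point rise moves overall detection by 1.9 points. Erasing the planned 3.3-point gap needs 3.3 / 0.647 = 5.1 points.
- T = 0.55: s = 0.138. A 3-point rise moves it by 2.6 points. Erasing the gap needs 3.3 / 0.862 = 3.8 points.

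**The case against.** The strongest reply is that the article never says the operator knows the arm during targeting. The sentence in 2.2 concerns results. The wording that systematic cores are then arranged also fits disclosure after the targeted cores. The flowchart in Figure 1 is not reproduced here, and a journal article commonly leaves the mechanics of allocation release to the full protocol. This stands as far as it goes: unblinded targeting is an inference. What remains is that the only stated reason for non-blinding does not reach allocation, and that the described order leaves an easy safeguard unused or unmentioned.

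The reply also holds that bias is speculative. Targeting is fixed at three cores in one small lesion, no evidence shows that operators vary by arm, and the effect could run either way. This stands too, and the figures above are therefore scenarios.

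A reader might infer two stronger points that the article does not support.

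- That a 3-point gain in targeted yield in Group A would cancel the planned 3.3-point gap. It would not: 3 is less than 3.3, and step 5 shows that 3.8 to 5.1 points would be needed under the assumed targeted yields.
- That opening the allocation late removes loss before biopsy. A sealed assignment made earlier and opened late leaves men who are never biopsied in the randomised set. Only randomising after the third core keeps them out. If the full 10% were lost before biopsy, 280 × 0.9 / 2 = 126 per arm would have the outcome instead of 140, with power of 78.4% against 82.5% at the assumed 20-point margin. The article does not say how much of the 10% falls before biopsy. Withdrawal is allowed at any time, follow-up runs to week 4, and Table 1 does not say whether the men not biopsied had already been randomised.

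**Conclusion.** The point holds in a limited form. The stated rationale covers MRI and clinical data only, and no blinding to the arm is described for three operator-dependent cores that both groups share and that count in the primary outcome. If the arm is known then, a difference in targeting between groups is possible. The version that favours Group A is anti-conservative for a trial meant to support fewer cores: about 3.6% to 5.2% one-sided type I error in place of 2.5% for a shift of 1 to 2 points in overall detection.

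This rests on three assumptions: early disclosure, a non-inferiority reading with an unstated margin, and a shift whose size and direction are unknown. Any power gain from later randomisation is a possible side benefit of unknown size. The change is worth making because it is cheap and leaves the biopsy as described, although no bias has been shown.

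**What to change.** In sections 2.2 and 2.4.2, state that the operator has the MRI and clinical data but is blind to allocation until the third targeted core has been taken. Preferably randomise at that moment, online or by sealed opaque envelope, for all men still to be enrolled. If randomisation stays earlier, say so and say how the arm is concealed until then.

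Add a comparison of targeted-only detection between groups as a check on equal targeting. The separate labelling of cores already allows it, and it can also be applied to men already biopsied.

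The cost is releasing the allocation in the biopsy room and preparing containers for both templates each time. The required number per group does not change. The operator remains unblinded for the systematic cores, and this change does not address that.

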**Figure 1 F1:**
[figure not shown]
Patients selection flowchart.

### Study participants

2.3.

Patients will be considered eligibly recruited if they fulfill the following inclusion criteria: (1) Men ≥18 years old with clinical suspicion of PCa (i.e., abnormal digital rectal examination or elevated PSA, PSA ≥ 4 ng/ml); (2) serum PSA level ≤20 ng/ml, clinical stage ≤cT2; (3) Prebiopsy mpMRI performed within 3 months and patients with only solitary MRI lesion (maximal diameter <2 cm) on mpMRI (PIRADS score >2). The exclusion criteria are as follow: (1) men with previous prostate biopsy; (2) prior treatment for prostate; (3) mpMRI done elsewhere; (4) any contraindications for biopsy, such as coagulation disorders, severe internal and external hemorrhoids; (5) patients not willing to write informed consent. Participants can stop participating the study at any time for any reason. Data until the time of withdrawal can be included in the study.

### Interventions and outcomes

2.4.

#### Multiparametric MRI procedures

2.4.1.

Multiparametric MRI will be carried out using a 3.0 T MRI system (Skyra, Siemens, Germany or GE Healthcare, USA). Supplementary Table S1 shows different MRI protocols. High resolution T2-weighted, diffusion-weighted, and T1-weighted dynamic contrast-enhanced imaging will be acquired through the MRI protocol. A radiologist (minimal 5-year experience) will describe the mpMRI findings using the PIRADS v2.1.

#### TRUS biopsy

2.4.2.

TRUS guided transperineal prostate biopsy will be performed under local anesthesia by experienced urologists. Three cores of cognitive fusion TBx were performed within the index lesion (defined as the lesion with the highest PIRADS v2 score, or the lesion with the maximal diameter if more than two lesions with the same score). Then, 6-core or 12-core SBx will be arranged for the patients according to the enrollment (Figure 2). The standard 12- core systematic sampling protocol will be performed transperineally with five cores distributed evenly through the left and right peripheral zones, and another core will be further spread on left and right transitional zones (10). Each core will be labeled independently and sent to histology using separate containers.

**Figure 2 F2:**
[figure not shown]
Prostate biopsy scheme.

#### Outcome

2.4.2.

The primary outcome compares the detection rate of PCa and csPCa between group A and group B where csPCa is defined using the Gleason scoring system (Gleason ≥3 + 4) (11). The secondary outcomes conclude as follow: (1) The yield of clinically significant prostate cancer on each side of prostate comparing it to side of lesions (contra- or ipsilateral to lesions). (2) The PCa and csPCa detection rate when adding transitional zone cores (11 and 12 cores in total). (3) The PCa and csPCa detection rate between Group A and 10-core SB plus 3-core TB in Group B. (4) The PCa and csPCa detection rate between transitional zone and peripheral zone in Group A and Group B. (5) Comparing the participant-reported pain score immediate post biopsy using pain measurement scale (Supplementary Figure S1). (6) proportion of men with post-biopsy complications and adverse events (Time frame: 7 days post biopsy, 30 days post biopsy), which include pain, fever, urinary infection/prostatitis needing antibiotics, urinary retention, erectile dysfunction, urinary incontinence, haematochezia, haematuria, and haemotospermia. (7) proportion of the men who undergo radical prostatectomy and have cancer upgraded histopathology from the biopsy to the radical prostatectomy (Table 1).

**Table 1 T1:** Schedule of record.

	Visit 0	Visit 1	Visit 2	Visit 3
Weeks	−1	0	1	4
Teleconsult	×		×	×
Inclusion/Exclusion	×			
Family history of prostate cancer	×			
Informed consent	×			
Age	×			
t-PSA level	×			
free/total PSA ratio	×			
mpMRI result	×			
Number of lesions	×			
Size of lesions	×			
Index lesion PIRADS score	×			
Biopsy outcome			×	
Benign tissue			×	
Atypical small acinar proliferation			×	
High-grade prostatic intraepithelial neoplasia			×	
Clinically insignificant cancer			×	
Clinically significant cancer			×	
Positive biopsy cores			×	
Gleason score			×	
Men who did not undergo biopsy		×		
Undergo surgery				×
Surgery outcome				×
Pathology Gleason score				×
Immediate post biopsy questionnaire (pain)		×		
Complications		×	×	×

### Sample size estimation

2.5.

We calculated sample size according to our results of retrospective database. Based on a power of 80% and a 2.5% one-sided *α*, we used an estimate for detection rate of PCa for 6-core systematic plus 3-core MRI-targeted prostate biopsy of 61.2% and an estimate of detection rate for 12-core systematic plus 3-core MRI-targeted prostate biopsy of 64.5%. Thus, 132 men per group will be required. Accounting for a dropout rate of 10%, 280 men will need to be recruited.

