Although targeted biopsy alone using far less biopsy cores detected no less Gleason ≥3 + 4 and fewer Gleason 6 cancers when compared with SBx, it may still inevitably underestimate a proportion of high-grade PCa in comparison with the combined approach (5, 6, 21). Previous study indicated that when using a combined SBx and targeted biopsy as a reference, directly omitting SBx resulted in detecting 13% less csPCa (7). Therefore, as strongly recommended by EAU guideline, combining targeted biopsy and SBx remains the optimal choice currently (2, 22). As previously reported, the suitable cores for the targeted and SBx have been separately investigated. Notably, how to keep the total cores (SBx plus target biopsy) lower while optimize the detection rate of csPCa is another urgent problem in the era of combined biopsy.

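### The 132 men per group does not follow from the stated rates, alpha and power: for the difference test that is planned it gives about 8% power, and it is reproduced by a 20-point non-inferiority margin that the article never states

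*Protocol article*

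**What the plan says.** The sample size paragraph (section 2.5) sets its error rates with "Based on a power of 80% and a 2.5% one-sided" alpha. It takes a "detection rate of PCa for 6-core systematic plus 3-core MRI-targeted prostate biopsy of 61.2" per cent for Group A and, for Group B, a "detection rate for 12-core systematic plus 3-core MRI-targeted prostate biopsy of 64.5" per cent, both from the sponsor's retrospective data. It then goes directly to "Thus, 132 men per group will be required" and adds: "Accounting for a dropout rate of 10%, 280 men will need to be recruited". Allocation is "with a ratio of 1:1" (section 2.2). No null hypothesis and no margin is given there or elsewhere in the article.

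Section 2.6 compares categorical outcomes between the groups by a chi-square or Fisher exact test of a difference, with significance at two-sided P < 0.05. It describes no non-inferiority analysis. The primary outcome in section 2.4 covers detection of both PCa and csPCa; the sizing uses PCa only.

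The Discussion, citing an earlier study, reports that "directly omitting SBx resulted in detecting 13% less csPCa".

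**The concern.** A reader who takes the section at face value will believe that the trial has 80% power for the comparison that section 2.6 describes. The two planning rates are only 3.3 points apart, and 132 per group is far too few to detect that. The number must therefore come from another type of calculation that the article does not name.

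This bears on the main conclusion. The trial asks whether six systematic cores can stand in for twelve. With a two-sided difference test, the likely result under the planning assumptions is a non-significant P value, which is easily taken as evidence that the two schemes are equivalent. With a non-inferiority test, the conclusion depends almost wholly on the margin, and the reader is not told what it is.

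**Working it through.** **Inputs.** From section 2.5: p_A = 0.612, p_B = 0.645, one-sided alpha 0.025 (z = 1.960), power 80% (z = 0.8416), 132 per group, 280 in total, 10% dropout. From section 2.2: 1:1 allocation. From section 2.6: two-sided 5% test, which has the same critical value of 1.960.

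Variance term: v = 0.612 × 0.388 + 0.645 × 0.355 = 0.4664. Multiplier: (1.960 + 0.8416)² = 7.849.

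**1. Reproducing 132 as a difference test.** n = 7.849 × 0.4664 / 0.033² ≈ 3,362 per group. The pooled-variance formula gives 3,365, and 3,425 with continuity correction. Changing alpha does not help: one-sided 5% gives 2,651 and two-sided 2.5% gives 4,075. No version comes near 132.

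**2. Power of 132 per group for that difference.** Standard error = √(0.4664/132) = 0.0594. Power in the expected direction = Φ(0.033/0.0594 − 1.960) = 8.0%. Counting rejections in both tails gives 8.6%.

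**3. Reproducing 132 as a non-inferiority test.** Solving for the margin: 0.033 + √(7.849 × 0.4664/132) = 0.1995. With a margin of 0.20, n = 7.849 × 0.4664 / (0.20 − 0.033)² = 131.3, which rounds up to 132. The Farrington–Manning formula gives 129 at the same margin. Smaller margins need more men per group: 268 for 15 points, 390 for 13 and 816 for 10.

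**4. Other routes to about 132.** A margin of 16.5 points works if no true difference is assumed; 13.4 points works if the expected difference has the opposite sign; about 18 points gives 134 at one-sided 5%. Each conflicts with a stated rate or with the stated alpha, and the first two margins are not round figures.

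**5. What a 20-point margin would mean.** 64.5 − 20 = 44.5%, a relative loss of 20/64.5 = 31%.

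**6. Power for the numbers recruited.** 280 men is 140 per group, and 280 × 0.9 / 2 = 126 per group after the stated dropout. (To keep 132 after 10% dropout, 132/0.9 = 147 per group would be needed.) Power = Φ((margin − 0.033)/√(0.4664/n) − 1.960):

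| Margin (points) | n = 126 | n = 132 | n = 140 |
|---|---|---|---|
| 20 | 78% | 80% | 82% |
| 15 | 49% | 50% | 53% |
| 13 | 36% | 37% | 39% |
| 10 | 20% | 20% | 21% |

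**7. Precision.** The 95% confidence interval half-width is 1.96 × √(0.4664/n): 11.9 points at 126 per group, 11.7 at 132 and 11.3 at 140.

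**The case against.** The strongest reply is that this is a condensed article. The one-sided 2.5% alpha suggests non-inferiority, and the margin may stand in the full protocol or analysis plan. That is fair as far as a missing margin goes. It does not remove the problem, because the article presents a derivation whose result does not follow from the inputs shown, and section 2.6 plans a difference test, which conflicts with the reading that yields 132.

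Three stronger readings are tempting, and the documents do not support them.

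- *That the trial uses a 20-point margin.* This is the best-fitting round value, not a documented choice.
- *That the implied margin exceeds the loss from having no systematic cores at all.* The cited 13% concerns csPCa, while the sizing is on any PCa. The article does not say whether the 13% is absolute or relative, and the figure comes from another study whose population may differ. It gives a rough sense of scale and cannot set an upper limit for the margin.
- *That the trial cannot answer its question.* The question is 6+3 against 12+3 cores, there is no targeted-only arm, and the trial will still estimate that difference with a usable interval.

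**Conclusion.** The point stands in this form: 132 per group does not follow from the inputs given, and the claimed 80% power does not belong to the analysis that section 2.6 describes. For that analysis the shortfall is about 25-fold (3,362/132), with power near 8%. The 80% is recovered only by adding an unstated non-inferiority margin of about 20 points, and power falls to about a half at 15 points and a fifth at 10.

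These figures assume the planning rates of 61.2% and 64.5%, the normal approximation, 1:1 allocation and any PCa as the endpoint. They give no power for csPCa, because the article states no planning rates for it. The discrepancy is large enough that the choice of formula makes no difference to the conclusion. It should be corrected before the results are analysed, since the interpretation of the primary comparison depends on it.

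**What to change.** No extra recruitment is needed for this correction.

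1. In section 2.5, state the hypothesis being tested and the margin actually used, with its justification. If the csPCa figure in the Discussion is used as a benchmark, say that it refers to a different endpoint from the one sized.
2. In section 2.6, replace the two-sided difference test for the primary outcome with the matching analysis: a two-sided 95% confidence interval for the risk difference, compared with the stated margin. Say that a non-significant P value will not be read as equivalence.
3. Restate the power for the evaluable number (126 per group after 10% dropout, or 140 if nobody is lost) at the stated margin, from the table above.
4. If no defensible margin gives adequate power, remove the 80% claim and describe the trial as estimating the difference to about ±12 points.

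The cost is a change of wording in the protocol and, where the registration carries the same statements, there too. The sponsor will have to report a less favourable power or make a softer claim.

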### Statistical analysis

2.6.

In this study, the baseline characteristics will be summarized as the mean ± standard deviation (SD) or median (interquartile range, IQR) for continuous data and(percentages) for categorical data. We will use the univariable and multivariable logistic regression analysis to evaluate some potential predictors for csPCa (i.e., PSA density, age, prostate volume). We will use student's *t*-test for continuous variables and chi-square or Fisher exact test for categorical variables to compare the difference between group A and group B. The statistical software package R (http://www.R-project.org, The R Foundation, Boston, Massachusetts, USA) and EmpowerStats (http://www.empowerstats.com, X & Y Solutions, Inc., Boston, MA) will be used to conduct statistical analyses. All results of the analysis are considered to be statistically significant with a two-sided *P* < 0.05.

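### A recruitment target of 280 does not allow for 10% dropout on 132 men per group; it covers a loss of about 5.7%

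*Protocol article*

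**What the plan says.** Section 2.5 (Sample size estimation) sets the error rates: "Based on a power of 80% and a 2.5% one-sided" α. It assumes a prostate cancer detection rate of 61.2% in Group A (6 systematic plus 3 targeted cores) and 64.5% in Group B (12 plus 3 cores). It concludes: "Thus, 132 men per group will be required". The next sentence gives the recruitment target: "Accounting for a dropout rate of 10%, 280 men will need to be recruited".

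The Methods paragraph of the abstract repeats the total: "280 men meeting inclusion criteria will be recruited and will be randomly allocated". So 280 is the number randomised, before any losses. Section 2.2 gives 1:1 allocation, hence 140 per group.

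The article contains no other dropout rate and no rule for replacing men who leave. Section 2.3 allows data collected before withdrawal to be used. Table 1 has a line for men who were not biopsied.

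**The concern.** Section 2.5 prints all three numbers in the chain: the requirement (132 per group), the expected loss (10%) and the resulting target (280). They cannot all be right. This is not detail that an article leaves to a fuller document, because no fuller document can make the three printed figures consistent.

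What is at stake is the meaning of the requirement. The protocol ties 80% power to 132 men per group. Under its own dropout assumption it would have fewer than that. The figure of 280 is also the headline target, given in both the abstract and the methods, so the claim that it includes a 10% allowance is likely to be carried into the trial report.

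**Working it through.** **Inputs** (section 2.5 unless noted): 132 per group; 1:1 allocation (section 2.2), so 264 in total; dropout d = 0.10; recruitment target 280; detection rates 0.612 and 0.645; one-sided α = 0.025; power 80%.

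**1. Attempt to reproduce 280.**

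| Rule | Calculation | Total |
|---|---|---|
| N/(1 - d) | 264/0.9 = 293.3 | 294 (147 per group) |
| N x (1 + d) | 264 x 1.1 = 290.4 | 291 (292 if rounded up by group) |
| Protocol | – | 280 |

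Neither rule gives 280. The gap is 294 - 280 = 14 men, or 291 - 280 = 11 men, too large to be rounding.

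**2. What 280 does cover.** 1 - 264/280 = 0.057, so 5.7% loss.

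**3. What remains at 10% loss.** 280 x 0.9 = 252, or 126 per group. That is 132 - 126 = 6 short per group, 12 in total.

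**4. Effect on power.** This step needs an assumption, because section 2.5 states no margin and does not say which comparison gave 132.

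- A test for a difference between 61.2% and 64.5% would need 3365 per group, and 132 per group would give about 8% power. So 132 did not come from that calculation.
- The usual non-inferiority formula is n = (1.960 + 0.842)² x V / (M - 0.033)², where V = 0.612 x 0.388 + 0.645 x 0.355 = 0.4664, M is the margin, and 0.033 = 0.645 - 0.612. With M = 0.20 this gives 7.849 x 0.4664 / 0.167² = 131.3, so 132. Other margins give other numbers: 816 per group at 10 points, 268 at 15 and 117 at 21.

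A margin of 20 points therefore reproduces 132, but it is inferred from the result and does not stand in the article. Power is Φ((M - 0.033)/√(V/n) - 1.960):

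| Assumed margin | Power at 132 | Power at 126 | Loss (points) |
|---|---|---|---|
| 20 points | 80.2% | 78.4% | 1.8 |
| 15 points | 50.3% | 48.5% | 1.8 |
| 10 points | 20.2% | 19.5% | 0.7 |

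If the margin is instead solved to give exactly 80% at 132 (19.95 points), power at 126 is 78.1%, a loss of 1.9 points. In every case shown, going from 132 to 126 per group costs less than 2 points.

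**The case against.** **The shortfall is conditional.** Because 280 exceeds 264, the requirement is met unless more than 5.7% are lost. This stands. A reader might infer that the stated 80% power is simply not met, and the article does not support that: the shortfall arises only if losses reach the planned rate.

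**Fewer than 10% may be lost to the primary outcome.** Table 1 places the biopsy visit at week 0 and the biopsy result at week 1, and section 2.3 keeps data up to withdrawal. A man lost to the week 4 contact still counts for detection; one who is never biopsied does not. This also stands, and makes 126 per group the worst case under a 10% rate. It does not rescue the sentence, since section 2.5 applies the 10% directly to the sample size for detection.

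**The power loss is small and rests on an assumed margin.** Correct on both counts. A reader might go further and infer that the dropout error leaves the trial badly underpowered, since power at 15 or 10 points is far below 80%. That low power is present at 132 per group before any dropout. It comes from how 132 was obtained, which is a separate question. Just below 20 points the fall is not dramatic either: at 19 points, power at 126 per group is about 73%.

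**Conclusion.** The point holds as an arithmetic contradiction within section 2.5. With 132 per group and 10% dropout the target is 294 (291 by the shortcut), not 280; and 280 allows for about 5.7%. These results use only printed figures.

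If 10% are lost to the primary outcome, the trial has 126 per group and slightly misses the power that it ties to 132. That direction follows from the protocol's own requirement. The size does not: it is under 2 percentage points on the assumed 20-point margin, and the document offers no margin with which to confirm this. No endpoint, test or comparison is altered. The correction is worth making because the figure is a headline one and the error is certain, but its practical effect is modest.

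**What to change.** Keep 280 and correct the last sentence of section 2.5 in one of two ways:

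- state that 280 men allow for a dropout of about 5.7% on 132 per group; or
- state that a 10% dropout would leave 126 per group, below the required 132.

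Do not add a restated power, such as 78%, unless the margin behind 132 is also stated; otherwise the new figure would rest on an assumption that the protocol does not contain.

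The cost is one sentence and a slightly less favourable statement of the allowance. Recruitment and the total in the abstract stay as they are. Keeping both the 10% allowance and 132 per group would instead mean a target of 294, which is 14 more men.
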